[figure not shown]

# CONSORT

TRANSPARENT REPORTING of TRIALS

## CONSORT 2010 Flow Diagram

[figure not shown]

## Introduction

Raised blood pressure (BP) is established as a strong independent risk factor for cardiovascular diseases (CVD), accounting for 70% of strokes and 50% of myocardial infarction in China. On the one hand, previous investigations have reported the low level of awareness, treatment, and control of hypertension in China. However, most surveys were community based and were conducted among the general population, few reported the current prevalence and management of hypertension among the working population, and no data are available about their variations by occupation, sector, workplace ownership and medical resources. Reliable information on variations in hypertension prevalence by sex, occupation, industry classifications, etc., among Chinese working adults is crucial for developing workplace-based strategies for prevention and control of this condition.

On the other hand, from the international perspective, workplace-based intervention could be a potent approach to assist patients with uncontrolled HTN to reach BP goals.

It is well known that appropriate BP control in the hypertensive patients by lifestyle and pharmaceutical interventions can reduce CVD events effectively, while the substantial proportion remains uncontrolled. However, few studies have been specifically designed to address the HTN control among Chinese working population. Most of previous studies have been limited by small sample sizes and did not report the effectiveness of intervention on specific subgroups. Additionally, these studies did not link BP control with individual and workplace factors simultaneously.

As recommended by American Heart Association (AHA), workplace wellness programs are an important strategy to prevent major risk factors for CVD. Therefore, we will conducted a standardized management of hypertensive employees' program, aiming to assess the prevalence, awareness, treatment, and control of hypertension among the Chinese working population, and to develop a multicomponent intervention strategy that combined workplace health promotion and standardized management of hypertensive employees to improve BP control, based on the baseline survey. Herein, we hypothesize that this intervention program could improve BP control in workplaces across China, and a cluster-controlled trial will be conducted to test this hypothesis.

**Primary Objective:** Assess the change in the percentage of patients with controlled BP from baseline to the 24-month follow-up.

**Secondary Objective(s):**

- Assess the changes of BP level from baseline to the 24-month follow-up.
- Assess the changes in prevalence of smoking, drinking, exercise, and overweight/obese, from baseline to the 24-month follow-up.

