**Exploratory Objective(s):**

- Assess the intervention effect across the subgroups of education, occupation status, workplace ownership, and workplace-affiliated hospital.

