### **Effectiveness assessments**

There will be two examinations for both groups, at baseline and 24 months (after 2 years intervention). Indicators including BP, BMI and lifestyle factors will be assessed.

All outcome assessments will be conducted at baseline and at 24-month follow-up in exactly the same way in the clinics for all patients, irrespective of their assignment to intervention or control group. For the intervention patients, monthly follow-up visits will be made within the 2 years duration to document the BP and lifestyle factors.

177

178 **Statistical Methods:**

179 All patients who attended follow-up visits at 24 months and had complete data for the  
180 primary outcome and other variables were included in the analysis. The baseline  
181 differences between patients included and unincluded, patients in the intervention  
182 group and those in the control group, will be examined by mixed-effects model. All  
183 patients who attend follow-up visits at 24 months and have complete data for the  
184 primary outcome may be included in the analysis, without imputation for missing data.  
185 The intervention effect will be performed as the difference between two groups, it will  
186 be calculated as intervention (values at 24 months minus values at baseline) minus  
187 control (values at 24 months minus values at baseline), and evaluated by  
188 mixed-effects models (PROC MIXED for continuous variables, PROC GLIMMIX for  
189 categorical variables), which included a random cluster effect (workplace). Group  
190 (intervention, control), all the baseline covariates, and potential interaction terms were  
191 used for adjustment in all models. The subgroup analyses of primary outcome will be  
192 conducted to assess the intervention effect on subgroups of education, occupation  
193 status, workplace ownership, and workplace-affiliated hospital. To evaluate the  
194 robustness of the results of the primary analyses, multiple-imputation method was  
195 adopted to handle missing data on outcome and covariates in a sensitivity analysis.  
196 The results will be summarized as rate (%), mean, standard deviation (SD), standard  
197 error (SE), and 95% confidence interval (CI) when appropriate. All data analyses will  
198 be conducted using SAS 9.4 (SAS institute, Cary, NC, USA) and a two-sided *P*-value

<0.05 will be considered statistically significant.

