
299

300 **Appendix B: Questionnaire (For Baseline and 24 month)**

301 Sub-center ID \_\_\_\_\_ No. of work unit \_\_\_\_\_ No. of employee \_\_\_\_\_

302 Section A: Basic information

303 A1. Name: \_\_\_\_\_

304 A2. Gender: ①Male ②Female

305 A3. Race: \_\_\_\_\_

306 A4. Occupation: ①Managerial ②Professional technical ③Clerical

307 ④Sales and services ⑤Workers ⑥Others\_\_\_\_\_

308 A5. Date of birth: Year\_\_\_\_\_ Month \_\_\_\_\_ Day \_\_\_\_\_

309 Section B: Health status (Determined according to the current Chinese clinical

CONFIDENTIAL

Division of Prevention and Community Health, National Center for Cardiovascular Disease, China

310 guidelines)

311 B1. Do you have hypertension? ①No ②Yes ③Unclear

312 If yes, the duration is: \_\_\_\_\_years; Current BP levels (SBP/DBP):

313 \_\_\_\_\_/\_\_\_\_\_mmHg

314 Do you take the BP-lowering drugs currently? ①No ②Yes

315 B2. Do you have dyslipidemia? ①No ②Yes ③Unclear

316 If yes, the duration is: \_\_\_\_\_years; Current total cholesterol (TC): \_\_\_\_\_

317 mmol/L

318 or \_\_\_\_\_ mg/dL

319 Do you take the TC-lowering drugs currently? ①No ②Yes

320 B3. Do you have diabetes? ①No ②Yes ③Unclear

321 If yes, the duration is: \_\_\_\_\_years; Current fasting blood-glucose (FBG): \_\_\_\_\_

322 mmol/L or \_\_\_\_\_ mg/dL

323 Do you take the FBG-lowering drugs currently? ①No ②Yes

324 B4. Do you have myocardial infarction? ①No ②Yes ③Unclear

325 If yes, the duration is: \_\_\_\_\_years.

326 B5. Do you have stroke? ①No ②Yes ③Unclear

327 If yes, the duration is: \_\_\_\_\_years.

328 Section C: Family history (Positive is defined as parents/siblings suffer from the

329 diseases before the age of 50 years)

330 C1. Hypertension ①No ②Yes ③Unclear

331 C2. Stroke ①No ②Yes ③Unclear

- 332 C3. Coronary heart disease      ①No   ②Yes   ③Unclear
- 333 C4. Diabetes      ①No   ②Yes   ③Unclear

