- 334 Section D: Lifestyle factors
- 335 D1. Do you prefer eating salty food regularly?      ①No   ②Yes
- 336 D2. Do you perceive high levels of stress recently?   ①No   ②Yes
- 337 D3. Do you smoke currently (at least one cigarette per day)? ①No   ②Yes
- 338      If yes, how many cigarettes do you smoke daily on average? \_\_\_\_\_
- 339 D4. Do you drink currently (consumption of at least 1 alcoholic beverage per week)?
- 340      ①No   ②Yes
- 341      If yes, how many times do you drink per week on average? \_\_\_\_\_
- 342 Section E: Physical examination and Biochemical test
- 343 E1. Height: \_\_\_\_\_ cm; Weight: \_\_\_\_\_ kg
- 344 E2. Blood pressure (SBP/DBP):
- 345      The first time \_\_\_\_/\_\_\_\_ mmHg; the second time \_\_\_\_/\_\_\_\_ mmHg;
- 346 E3: Fasting glucose: \_\_\_\_\_ mmol/L or \_\_\_\_\_ mg/dL
- 347 E4: Triglycerides: \_\_\_\_\_ mmol/L or \_\_\_\_\_ mg/dL
- 348 E5: Total cholesterol: \_\_\_\_\_ mmol/L or \_\_\_\_\_ mg/dL
- 349 E6: High density lipoprotein cholesterol: \_\_\_\_\_ mmol/L or \_\_\_\_\_ mg/dL
- 350

351      **Appendix C: Questionnaire (For monthly follow-up in intervention group)**

352      Sub-center ID \_\_\_\_\_      No. of work unit \_\_\_\_\_      No. of employee \_\_\_\_\_

353      Section A: Physical examination

*CONFIDENTIAL*

*Division of Prevention and Community Health, National Center for Cardiovascular Disease, China*

354 A1. Blood pressure (SBP/DBP):

355 The first time \_\_\_\_/\_\_\_\_ mmHg; the second time \_\_\_\_/\_\_\_\_ mmHg;

356 Section B: Lifestyle factors

357 B1. Do you prefer eating salty food regularly? ①No ②Yes

358 B2. Do you perceive high levels of stress recently? ①No ②Yes

359 B3. Do you smoke currently (at least one cigarette per day)? ①No ②Yes

360 If yes, how many cigarettes do you smoke daily on average? \_\_\_\_\_

361 B4. Do you drink currently (consumption of at least 1 alcoholic beverage per week)?

362 ①No ②Yes

363 If yes, how many times do you drink per week on average? \_\_\_\_\_

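### Change in exercise is a secondary outcome, but the form for baseline and 24 months has no exercise item; education, a subgroup factor, is missing too but can be collected later

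*Protocol*

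**What the plan says.** Under Secondary Objective(s) the Protocol plans to "Assess the changes in prevalence of smoking, drinking, exercise, and overweight/obese, from baseline to the 24-month follow-up". Under Exploratory Objective(s) it plans to "Assess the intervention effect across the subgroups of education, occupation status, workplace ownership, and workplace-affiliated hospital". Statistical Methods repeats the subgroup plan for the primary outcome: analyses are "conducted to assess the intervention effect on subgroups of education, occupation" status and the two workplace factors. The same section defines each intervention effect as the 24-month-minus-baseline change in the intervention group less the same change in the control group.

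On measurement, Effectiveness assessments says only that "Indicators including BP, BMI and lifestyle factors will be assessed", at baseline and 24 months in both groups. The instrument is headed "Appendix B: Questionnaire (For Baseline and 24 month". Its demographic part, "Section A: Basic information", has five items (A1 to A5), one of which is "A4. Occupation: ①Managerial ②Professional technical ③Clerical" and further occupational categories. Its lifestyle part (Section D) has four items and ends with "D4. Do you drink currently (consumption of at least 1 alcoholic beverage per week". Appendix C is the monthly form for the intervention group.

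**The concern.** A change-from-baseline outcome needs the same variable, defined in the same way, at both time points and in both groups. The objectives promise this for exercise, but the questionnaire carrying the baseline and 24-month label does not ask about it. A statistical analysis plan can define or derive variables, but it cannot supply values that no form captured.

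The timing makes the exercise gap hard to repair. Physical activity is one of the seven parts of the workplace programme, so exercise measured after the start is already exposed to the intervention, and only recall could stand in for baseline. Baseline values also matter more than usual here: workplaces are matched and then assigned with the approval of their managers, so a 24-month difference alone could reflect a difference that was there from the start.

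The Protocol also gives no definition of exercise. The smoking and drinking items carry their own thresholds; without one for exercise there is no prevalence to compute.

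Education raises a smaller version of the same problem: it is named as a subgroup factor, but the form has no field for it.

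**Working it through.** No arithmetic beyond counting applies. The check sets each promised outcome and subgroup factor beside the items on the two forms.

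| Variable | Where promised | Source in Appendix B |
|---|---|---|
| Blood pressure level | Secondary Objective(s) | E2 |
| Smoking | Secondary Objective(s) | D3 |
| Drinking | Secondary Objective(s) | D4 |
| Overweight/obese | Secondary Objective(s) | derived from height and weight, E1 |
| Exercise | Secondary Objective(s) | none |
| Occupation | Exploratory Objective(s) | A4 |
| Workplace ownership | Exploratory Objective(s) | not on the form; a workplace fact, linkable through the work unit number |
| Workplace-affiliated hospital | Exploratory Objective(s) | not on the form; linkable in the same way |
| Education | Exploratory Objective(s), Statistical Methods | none |

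**Could an item have been lost when the PDF was read?** Not in the two sections that matter. In Appendix B, Section A occupies printed lines 302 to 308 and Section B starts at 309. Section D occupies 334 to 341 and Section E starts at 342. Item numbers also run on without a gap, from A1 to A5 and from D1 to D4.

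**Could Appendix C supply the data?** Its visible items are blood pressure, salty food, stress, smoking and drinking. It ends where the supplied text ends, so line numbers cannot rule out a further item. That does not change the result, because it is a monthly follow-up form for the intervention group and gives no control data.

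**Does the rest of the Protocol name a source?** Exercise and physical activity appear elsewhere only as parts of the workplace programme, and health education only as something delivered to employees. Effectiveness assessments refers to lifestyle factors in general, and Section D of Appendix B is the list with that title.

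**Count.** Of the four lifestyle and weight measures in the secondary objective, three have a source and one (exercise) has none. Of the four subgroup factors, three have a source or can be linked and one (education) has none.

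**The case against.** Several points on the other side are fair.

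- **Other forms may exist.** The appendices shown start at B, and the content of Appendix A is unknown. Study design also describes a first-phase cross-sectional survey, and the Protocol does not say whether Appendix B is the whole instrument for it. A reader might infer that Appendix B is the only patient form and that no patient will have exercise data. The documents do not establish that. They show that the form labelled for the two outcome visits lacks the item and that no other source is named. Even if the first-phase survey held baseline exercise, nothing shown supplies the 24-month value.
- **Education can be recovered.** A reader might infer that the education subgroup analysis is impossible. It is not. Education is stable in adults, the analysis uses patients who attend at 24 months, and the question can be put to them then. Employer records are another possible source.
- **Loss as a covariate is not shown.** A reader might also infer that adjustment for education is lost. Statistical Methods refers to the baseline covariates without listing them, and education is never named as one.
- **The primary analysis is intact.** Blood pressure control, blood pressure level, smoking, drinking and overweight/obese all have source items, and neither the sample size nor the primary model depends on the missing fields.

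These points limit the reach and severity of the finding. They do not remove the exercise gap: a stated objective has no item on the form designated for the visits at which it would be measured.

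**Conclusion.** The point holds for exercise. With the forms as written, the change in exercise prevalence cannot be computed in either group, and a missed baseline value cannot be recovered once the programme has begun. This affects one of four lifestyle and weight measures. For education it holds only as a minor, repairable omission affecting one of four exploratory subgroup factors.

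The conclusion assumes that Appendix B is used as labelled and that no instrument outside the text shown collects exercise at both time points. If one does, naming it in the Protocol, with its definition of exercise, settles the matter. The primary outcome and the remaining secondary outcomes are unaffected. This should be fixed, but the main result does not depend on it.

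**What to change.** **If baseline has not been completed:** add to Appendix B, Section D, an exercise item with a stated threshold, in the yes/no plus weekly frequency format of D4, and add to Section A an education-level item. Alternatively, name the existing source that holds exercise at baseline and 24 months in both groups, and the source that holds education.

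**If baseline is already complete without exercise:** Sample Size Considerations describes 3,600 intervention and 1,200 control patients in the past tense, so this may be the case. Then withdraw the change-in-exercise objective openly and give the reason, or replace it with a between-group comparison of exercise at 24 months, labelled as unadjusted for baseline and measured with a defined item. Collect education at month 24.

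**Cost:** two questionnaire lines and two database fields, at an estimated one minute or so per patient. Under the fallback, the cost is a documented change to one secondary objective.

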**Exploratory Objective(s):**

- Assess the intervention effect across the subgroups of education, occupation status, workplace ownership, and workplace-affiliated hospital.

**Study design**

*CONFIDENTIAL*

*Division of Prevention and Community Health, National Center for Cardiovascular Disease, China*

The study is a two-phase design. First, a cross-sectional survey designed to evaluate the prevalence and management of hypertension among Chinese working population. Then, a cluster-controlled trial conducted to test the effect of a multicomponent intervention strategy on improving hypertension control in workplaces.

For this program, a coordinating center will be established at Fuwai Hospital, Beijing. Then, 20 urban medical institutions will be selected as sub-centers, representing various geographic locations in China. Subsequently, 2 to 4 workplaces will be recruited by each sub-center, to test the feasibility of the protocol in work settings, all of which should meet the following criteria: (1) more than 50 patients can be recruited per site; (2) workplaces within the same sub-center should be matched by sector, ownership, size, economic level and medical condition; (3) none similar programs were conducted before; (4) non-medical institutions; (5) agrees to participate in the program for a minimum of 2 years; (6) agrees to arrange at least one full-time or part-time project officer to execute the workplace wellness program; and (7) can select a designated hospital clinic for implementing the standardized HTN management for 2 years.

Within each sub-center, 1 to 3 workplaces will be assigned to the intervention group, and one workplace assigned to the control group, with approval from manager of each workplace. To minimize the potential imbalance between groups, workplaces assigned to the intervention and control group within each sub-center, should be matched by sector, ownership, size, economic level and medical condition. Within each sub-center, at least 50 potential participants will be selected and invited for

89 baseline assessments at each workplace, and the patients will be allocated to  
90 intervention or usual care in a 3:1 ratio.

91 For the intervention patients alone, there will be monthly follow-up visits within  
92 the 2 years duration by their physicians. Patients in the control group carry on with  
93 their usual health care.

94

95 **Study Duration:**

96 Subjects will receive intervention for a minimum of 24 months.

97

98 **Study Inclusion and Exclusion Criteria:**

99 **Inclusion Criteria:**

- 100 1. Subject has a clinical diagnosis of HTN;
- 101 2. Subject is aged 18 to 60 years;
- 102 3. Subject is under a fixed term employment contract;
- 103 4. Subject has provided signed consent form;
- 104 5. Subject agrees to participate in the study for the full 2 years duration.

105 **Exclusion criteria**

- 106 1. Subject has secondary hypertension;
- 107 2. Subject has acute myocardial infarction or stroke less than 3 months;
- 108 3. Women who self-reports being pregnant or within 3 months postpartum;
- 109 4. Subject with life expectancy of less than 2 years;
- 110 5. Subject with psychiatric illness, hearing difficulty, or physical incapacitation;

6. Subject is a healthcare provider.

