### **Sample Size Considerations:**

The study is designed as an effectiveness trial of active interventions, compared with the usual care group. On the basis of previous literature, we expected that 20% of patients in the control group would be properly controlled, whereas we expected patients in the intervention group to increase this to 50% control at 24-month follow-up. Considering the intervention benefits and ethical issues, the study was designed to recruit patients using a 3:1 ratio. Cluster randomization power analysis was performed for the two independent proportions, and with a 2.5% type I error and intra-cluster correlation coefficient (ICC) of 0.01, we estimated that a sample size of 3,000 intervention patients (cluster size 75) and 1,000 control patients (cluster size 50) would provide 90% power to detect an improvement of 25% in BP control between the two groups and allowing 20% loss to follow-up in each group. To ensure an enough power, 3,600 intervention patients and 1,200 control patients were recruited in this study.

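### The protocol describes no random step in assigning workplaces and makes assignment subject to manager approval, yet it reports a cluster-randomization power analysis and speaks of patients being allocated 3:1

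*Protocol*

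**What the plan says.** The Protocol's Study design section describes the second phase as "a cluster-controlled trial conducted to test the effect of a multicomponent intervention strategy"; the Introduction uses the same cluster-controlled label. In each of 20 sub-centers, 2 to 4 workplaces are recruited. One to three go to intervention, with "one workplace assigned to the control group, with approval from manager of each workplace". No sequence, draw or concealment is described. The safeguard against imbalance is that workplaces within a sub-center "should be matched by sector, ownership, size, economic level and medical condition".

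The same section ends its account of assignment by saying that patients go to "intervention or usual care in a 3:1 ratio", although the arms consist of whole workplaces. Sample Size Considerations then states: "Cluster randomization power analysis was performed for the two independent proportions".

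Three eligibility criteria bear on feasibility, and they apply to every recruited workplace, controls included. Each one "agrees to participate in the program for a minimum of 2 years" (criterion 5), "agrees to arrange at least one full-time or part-time project officer to execute the workplace wellness program" (criterion 6) and "can select a designated hospital clinic for implementing the standardized HTN management for 2 years" (criterion 7).

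Statistical Methods defines the effect as the change from baseline to 24 months in the intervention group minus the same change in controls. It is estimated by mixed models with a random workplace effect and adjustment for baseline covariates.

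**The concern.** A reader cannot tell from the protocol whether assignment is random, or whether the unit is the workplace or the patient. These are basic design features that decide what causal claim the trial can make.

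If a manager's approval of the arm is part of assignment, workplaces more committed to health promotion could end up in the intervention arm more often. The intervention depends on that commitment: the workplace component includes changes to cafeteria food, smoking rules, office layout and exercise breaks. None of the five matching features measures it, and the baseline questionnaire in Appendix B has no item on it, so neither matching nor adjustment addresses it directly. Recruiting more patients makes the estimate more precise but leaves this kind of bias unchanged.

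**Working it through.** **1. The statements side by side.** The design label (Introduction, Study design) says controlled, not randomised. The assignment sentence mentions manager approval and no chance mechanism. The power statement refers to cluster randomization. The 3:1 sentence refers to patients. No other sentence reconciles these.

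**2. The plan's own figure.** Inputs from Sample Size Considerations: 3,000 intervention patients in clusters of 75, 1,000 controls in clusters of 50, ICC 0.01, 20% loss, 2.5% type I error, 25-point improvement, 90% power.

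- Clusters: 3,000/75 = 40 intervention and 1,000/50 = 20 control.
- After 20% loss: 40 × 60 = 2,400 and 20 × 40 = 800 patients.
- Design effects: 1 + 59 × 0.01 = 1.59 and 1 + 39 × 0.01 = 1.39.
- Effective sizes: 2,400/1.59 ≈ 1,509 and 800/1.39 ≈ 576.

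For 20% against 45%, power is essentially 100% at two-sided 0.05 or 0.025, so the stated 90% does not reproduce. That is a separate matter on which this point does not depend. What matters here is that random error is small. The same formula serves any parallel comparison of clusters, so the word randomization is not an input to it.

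**3. Standard error under no effect.** With 20% controlled in both arms, p(1 − p) = 0.16:

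SE = √(0.16 × 1.59/2,400 + 0.16 × 1.39/800) = 0.0196, or about 2.0 points.

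This is for the month-24 comparison. The standard error of the planned difference in change needs a within-person correlation that the protocol does not give.

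**4. Illustration of bias.** Let b be a residual difference between arms not caused by the intervention. At the two-sided 5% level,

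P(false positive) = 1 − Φ(1.96 − b/SE) + Φ(−1.96 − b/SE).

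| Assumed b | b/SE | False-positive rate |
|---|---|---|
| 0 | 0 | 5% |
| 2 points | 1.02 | 18% |
| 2.5 points | 1.28 | 25% |
| 3 points | 1.53 | 33% |
| 5 points | 2.55 | 72% |

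The values of b are assumptions; the protocol offers none.

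**5. The same bias with a real effect.** With rates of 45% and 20%, SE = √(0.2475 × 1.59/2,400 + 0.16 × 1.39/800) = 0.0210. If 5 points of an observed 25-point difference were bias, 20 points would remain, and 0.20/0.0210 ≈ 9.5 standard errors. Added to a true 25-point effect, 5 points inflate it by 5/25, one fifth.

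**6. What randomising would do to power.** The implied 60 workplaces average three per sub-center, one of them control. Drawing that control at random adds no cluster and no patient. With a t reference on 60 − 20 − 1 = 39 degrees of freedom and 20% loss, power for 20% against 45% stays above 99.9% at ICC 0.01, 0.05 and 0.10, at two-sided 0.05 or 0.025. With three workplaces in each sub-center there would be 3^20, about 3.5 billion, possible allocations; with two in each, 2^20, about 1.05 million.

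**The case against.** The strongest reply is that this is an openly controlled, matched study that never calls itself randomised. The power sentence names a calculation, not the design, and the calculation is valid for non-randomised clusters too. Manager approval may mean no more than a gatekeeper's permission. The planned analysis compares changes, so stable differences between workplaces drop out. And the effect sought is far larger than any plausible selection difference.

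Much of this stands. The mismatch in the power sentence is one of label and of the basis for causal inference, not of arithmetic. That managers do steer assignment is not established; the text only leaves room for it. The difference in change answers stable differences, but not different trends in workplaces whose managers wanted the programme. The reply also leaves the reader without a stated method of assignment.

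Two stronger readings are tempting. A reader might infer from criteria 5 to 7 that every workplace has already agreed to either arm, so that randomising would cost almost nothing. Those criteria show readiness to join and run the programme; none records willingness to serve as a usual-care control. They also weaken the bias argument somewhat, because the more uniform the commitment, the less room for selection on it. A reader might also take the 72% as a forecast. It rests on an assumed 5-point bias, in a month-24 comparison, with no true effect.

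**Conclusion.** The point holds as a defect in how assignment is specified. The protocol describes no random mechanism, makes assignment subject to manager approval, and uses wording on randomization and on patient allocation that does not fit the rest. Followed as written, it allows selection that matching on five features does not address and that the difference in change addresses only in part.

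The size is unknown. Under no effect, an assumed 2.5 to 5 points of residual bias would turn a 5% false-positive rate into about 25% to 72%, given 20% control, ICC 0.01, 20% loss and a month-24 comparison. Against a true 25-point effect the same bias would inflate the estimate by a tenth to a fifth and would not reverse the conclusion. The protocol does not support saying that managers choose the arm, or that it declares the trial randomised.

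**What to change.** **If assignment is still open,** replace the assignment sentence with wording such as: *Once all workplaces in a sub-center meet the eligibility criteria and each manager has agreed in writing to accept either arm, the coordinating center draws the control workplace by computer within that sub-center. The workplace is the unit of allocation; 3:1 is the resulting ratio of patients.* Remove the statement that patients are allocated.

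The cost is one computer-generated list, a written agreement per workplace and a short amendment, with no added patients or clusters. The real downside is refusal. A workplace whose manager will not accept a draw must be replaced by one matched on the same five features. In a sub-center with only two workplaces, the comparison is lost until a replacement is found.

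**If assignment has already been made without randomisation** (Sample Size Considerations mentions recruitment in the past tense, though tenses are mixed throughout), describe the trial as non-randomised. Also remove randomization from the power statement, correct the patient-level wording, say how managers' approval entered the assignment, and limit the causal conclusion accordingly. This costs a wording amendment only, but leaves the possible bias in place.

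**If a random draw was in fact made** and approval meant permission only, say so and describe the draw.
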